## Abstract

**Background:**

Chronic fatigue with a debilitating effect on daily life is a frequently reported symptom among adolescents and young adults with a history of Q-fever infection (QFS). Persisting fatigue after infection may have a biological origin with psychological and social factors contributing to the disease phenotype. This is consistent with the biopsychosocial framework, which considers fatigue to be the result of a complex interaction between biological, psychological, and social factors. In line, similar manifestations of chronic fatigue are observed in chronic fatigue syndrome/myalgic encephalomyelitis (CFS/ME) and juvenile idiopathic arthritis (JIA). Cognitive behavioral therapy is often recommended as treatment for chronic fatigue, considering its effectiveness on the group level. However, not everybody benefits on the individual level. More treatment success at the individual level might be achieved with patient-tailored treatments that incorporate the biopsychosocial framework.

**Methods:**

In addition to biological assessments of blood, stool, saliva, and hair, the QFS-study consists of a randomized controlled trial (RCT) in which a single-subject experimental case series (*N=1*) design will be implemented using Experience Sampling Methodology in fatigued adolescents and young adults with QFS, CFS/ME, and JIA (aged 12–29). With the RCT design, the effectiveness of patient-tailored PROfeel lifestyle advices will be compared against generic dietary advices in reducing fatigue severity at the group level. Pre-post analyses will be conducted to determine relevance of intervention order. By means of the *N*=1 design, effectiveness of both advices will be measured at the individual level.

**Discussion:**

The QFS-study is a comprehensive study exploring disrupted biological factors and patient-tailored lifestyle advices as intervention in adolescent and young adults with QFS and similar manifestations of chronic fatigue. Practical or operational issues are expected during the study, but can be overcome through innovative study design, statistical approaches, and recruitment strategies. Ultimately, the study aims to contribute to biological research and (personalized) treatment in QFS and similar manifestations of chronic fatigue.

**Trial registration:**

Trial NL8789. Registered July 21, 2020.

**Supplementary Information:**

The online version contains supplementary material available at 10.1186/s13063-022-06620-2.

## Administrative information

Note: the numbers in curly brackets in this protocol refer to SPIRIT checklist item numbers. The order of the items has been modified to group similar items (see https://www.equator-network.org/reporting-guidelines/spirit-2013-statement-defining-standard-protocol-items-for-clinical-trials/)

## Introduction

### Background and rationale {6a}

Q-fever is a zoonosis caused by the intracellular gram-negative bacterium *Coxiella burnetii*. Severe chronic fatigue is a frequently reported complaint among patients with a history of Q-fever infection and is described as persistent or recurrent severe fatigue with a profound, debilitating effect on daily life [1, 2]. Especially in children, chronic fatigue affects future well-being and social participation [2, 3]. The most recent Q-fever epidemic took place in The Netherlands from 2007 to 2010 [4]. Since then, up to a dozen of new cases of Q-fever have been confirmed every year [5, 6]. Most of those affected with acute Q-fever recover from fatigue within 6 to 12 months [4]. Approximately 20% does not recover within this timeframe, leading to Q-fever fatigue syndrome (QFS) diagnosis [4, 7]. QFS has been associated with immune deregulation [8] and possibly mitochondrial dysfunction [9]; however, the etiology and pathophysiology of QFS is still largely unknown [8, 9].

The term QFS is derived from chronic fatigue syndrome (CFS), also known as myalgic encephalomyelitis (ME), because of its similar expression. Like with CFS/ME, individuals with QFS have, in addition to severe fatigue, a complex set of symptoms including, e.g., headache, muscle and/or joint strains, sore throat, and painful lymph nodes [6, 7, 10]. Post exertional malaise, unrefreshing sleep, memory or concentration difficulties, and issues regarding mental well-being, are also common [6, 7, 10]. As a result, daily functioning and participation in society are significantly limited [6, 7, 10].

An overlap in symptoms similar to QFS and CFS/ME is also observed in individuals suffering from fatigue in (auto-)immune diseases, such as juvenile idiopathic arthritis (JIA). Previous research has shown that severe fatigue is prevalent among 25% of individuals with pediatric rheumatic diseases [11], which is more prevalent than in the general population [2]. One systematic review reported fatigue among 60–75% of all JIA cases [12], and fatigue has been identified as a long-term sequela in 26% of JIA cases [13].

Fatigue is conceptualized as a generic symptom across diseases, instead of a disease-specific symptom [14]. Enck et al. hypothesized that medically unexplained functional symptoms following infection, such as fatigue, may have a biological origin, with psychological and social factors contributing to the disease phenotype [15]. This is consistent with the theoretical framework of the biopsychosocial model, in which fatigue can be seen as the result of a complex interaction between biological, psychological, and social factors [16, 17].

Even without knowing the exact primary biological events and subsequent cascades, the most promising treatment options for chronic fatigue are based on cognitive behavioural interventions (CBT) addressing dysfunctional cognitions, affect, physical activity, social support, or sleep patterns [18, 19]. Although CBT is effective on the group level [18, 19], it is not successful in all individuals. With regard to QFS, one study in adults showed positive effects on fatigue directly after CBT across subjects [20]—but without lasting effect for the majority at 1-year follow-up [21]. Further investigation on tailoring treatment to QFS was recommended [21].

We expect that it is even more effective to tailor treatment at the individual level, whilst incorporating the biopsychosocial perspective. This can be achieved by using experience sampling methodology (ESM), a method in which individuals receive multiple surveys per day for a longer period of time, resulting in the collection of highly intensive longitudinal data (ILD) [22]. ESM allows dynamic assessment of individual fatigue-perpetuating biological, psychological, and/or sociological factors, and has been implemented in PROfeel. PROfeel is a smartphone-based ESM method, followed by individual symptom network analysis, of which the results are used as starting point for face-to-face feedback and shared decision-making with the patient regarding lifestyle advice. The PROfeel method has been found feasible and useful by fatigued adolescents [23]. The next step is to test whether patient-tailored lifestyle advices based on the PROfeel method are also effective in reducing fatigue severity in the QFS-study.

The patient-tailored PROfeel lifestyle advices will be compared to generic dietary advices as potential treatment options. Nutritional advice has been effective in reducing medically unresolved fatigue symptoms in children before [24]. Based on an established relationship between the gut microbiome and fatigue, it is expected that a healthy diet positively influences the gut microbiome, potentially reducing fatigue [25].

In this paper, we describe the study objectives and methods of the QFS-study. The intervention part of the study consists of two designs. First, a randomized controlled trial (RCT), to compare the effectiveness of patient-tailored PROfeel lifestyle advices against generic dietary advices in reducing fatigue severity in adolescents and young adults with QFS, CFS/ME, and JIA at the group level. Second, a single-subject experimental case series (i.e., *N*=1) design to test the effectiveness of both advices at the individual level. The *N*=1 design will be implemented with PROfeel. Considering that the etiology and pathology of QFS is largely unknown, the QFS-study also includes biological research. Multiple biological assessments will be conducted to identify disrupted biological factors in participants with QFS, in comparison to participants with CFS/ME and JIA, or healthy controls.

### Objectives {7}

The first objective of the current study is to evaluate the effectiveness of patient-tailored PROfeel lifestyle advices and generic dietary advices as interventions on “fatigue severity”, “quality of life”, and “self-efficacy” on the group level. The second objective is to explore the same, but on the individual level for all participants (i.e., multiple *N*=1). If patient-tailored PROfeel lifestyle advices are effective, the third objective is to investigate through which mechanisms the effects have been reached, by exploring changes in the dynamic ESM networks pre-post intervention. The fourth objective is to explore the biological profile (e.g., immunological profile, HPA axis, mitochondrial dysfunction, and gut microbiome) of adolescents and young adults with QFS at baseline. Participants with QFS will be compared to participants with CFS/ME and JIA, as well as healthy controls. The fifth objective is to explore relationships between individual improvement differences in “fatigue severity” and subsequent changes in biological profile.

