### Intervention description {11a}

#### Patient-tailored PROfeel lifestyle advice

The RCT starts with a 4-week ESM assessment (see Table 1 for timeline). ESM is an innovative, validated, structured diary technique for longitudinal measurements of fluctuating states, that captures life as it is lived on the spot [22, 23, 29]. Multiple ESM applications are available for smartphones. In this study, we use the Ethica application (www.ethicadata.com) in which participants complete ESM surveys (i.e., diaries) approximately 5 times per day. In a first step, ESM data are used by a statistician to compute an individual descriptive report and an individual dynamic report with fatigue-perpetuating dynamic networks, identifying the contemporaneous and time-lag relations between fluctuations in fatigue and behavior, sleep, social context, cognitions, and feelings [23]. In a next step, the investigator uses the descriptive and dynamic reports to produce a reduced PROfeel report. Face-to-face, the investigator and participant discuss the PROfeel report and use shared decision-making to formulate a patient-tailored lifestyle advice. The term “lifestyle” here refers to an area of daily life that can be modified to potentially reduce fatigue and/or improve quality of life and self-efficacy. The combination of ESM with personalized feedback, leading to patient-tailored lifestyle advices, is named PROfeel. Details follow in the sections underneath.

**Table 1 Tab1:** Participant timeline in QFS-study

Week	Activity	Description
0	Screening	Evaluation of participant’s eligibility for the QFS-study by social pediatrician (and pediatric immunologist/rheumatologist in case of JIA diagnosis).
1	Study visit T0	Participant completes baseline KLIK questionnaires and installs the PROfeel app on smartphone to start ESM measurement. Participant also starts weekly measurement (of fatigue, quality of life, and self-efficacy) on smartphone which lasts throughout the study.
1-4	ESM phase I	Participant starts 4 weeks of ESM, with 5 surveys to answer per day. Surveys contain items inquiring after, e.g., fatigue and other symptoms, (social) activities, and affect in the last 3 h.
5	Study visit T1	Participant completes T1 KLIK questionnaires and is randomly allocated to either 12 weeks of patient-tailored PROfeel lifestyle advice or generic dietary advice. Biological samples (i.e., blood, stool, saliva, and hair) are collected for the first time.

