#### PROfeel: defining patient-tailored lifestyle advice

During shared decision-making, the investigator helps to define the lifestyle advice as feasible as possible. This is important since lifestyle advices often revolve around habits that need to be (re)learned. Because changing or learning habits is a slow process [30], the patient-tailored PROfeel lifestyle advices often represent a step in the participant’s process of (re)learning a habit. The advices incorporate factors known to strengthen habit learning, such as anticipating and avoiding self-control struggles, planning, and/or environment changes [30]. For example, when a participant struggles with rumination (i.e., worrying) throughout the day, an advice could be to reduce rumination time by practicing distracting attention. The investigator and participant could decide to work with a patient-tailored variation of “scheduled rumination” [31], in which the participant chooses a fixed timeslot to ruminate for 15 min, for instance, every day from 3:00 AM to 3:15 AM. To prevent self-control struggles, the participant and investigator compile a list of activities that help distract the participant from rumination. Whenever the participant finds him/herself ruminating outside the scheduled time, he/she is instructed to notice the thoughts, write them down if necessary, and divert attention with an activity on the list. Practicing scheduled rumination may lead to short-term improvement, provide insight in what the next step should be, and motivate the participant to take that next step in the long term.

Eventually, the patient-tailored PROfeel lifestyle advices will be adhered to for 12 weeks. During each week, the participant will receive a weekly survey on the Ethica app, inquiring about the levels of fatigue, quality of life, and self-efficacy in the past week, and whether he or she complied with the patient-tailored lifestyle advices.

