### Strategies to improve adherence to interventions {11c}

During the RCT, participants receive a boost from the investigator by phone and/or mail. Participants are also regularly reminded that they can contact the investigator for questions or help with their advice or technical problems with the app.

To improve adherence to the patient-tailored PROfeel lifestyle advices, the advices are formulated clearly and concretely (e.g., “cycle to school 3 days a week to increase physical activity” rather than “increase physical activity”). This way, participants know what is expected of them. Participants receive a weekly survey item on their smartphone, inquiring after their level of compliance.

To improve adherence to the generic dietary advice, participants receive a weekly survey inquiring after their compliance to each aspect of the dietary advice. The surveys function as both monitoring and reminder tools for the participant. Reminders are often used as a tool in behavior change interventions [30], and a meta-analysis has shown that reminders can make a small contribution to behavior change in dietary interventions [34].

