## Statistical methods

### Statistical methods for primary and secondary outcomes {20a}

To evaluate on the group level the effectiveness of the patient-tailored PROfeel lifestyle advices against generic dietary advices in reducing “fatigue severity” and improving “quality of life” and “self-efficacy” (objective 1), two statistical tests will be performed. The first test, is a 2 × 2 ANCOVA with “fatigue severity” at T2 as dependent variable, “fatigue severity” at baseline as covariate, and intervention condition as fixed factor. This test is used to compare the reduction in “fatigue severity” for the PROfeel-first group against the dietary-first group. The second test is a repeated measures 2 × 2 ANOVA to test whether the order in which participants received the advices is of relevance. The same tests will be performed for secondary outcomes “quality of life” and “self-efficacy”.

To evaluate the effectiveness of the patient-tailored PROfeel lifestyle advices and generic dietary advices in reducing “fatigue severity” and improving “quality of life” and “self-efficacy” at the individual level (objective 2), the permutation distancing test (PDT) will be used. This test is currently under development (see supplement of 41). This test takes into account autocorrelation, handles missing data by making optimal use of all observations, and is specifically developed for *N*=1 designs with a fixed intervention start.

To explore individual effects on pre-post intervention change in the dynamic networks for the participants who first receive patient-tailored PROfeel lifestyle advices first (objective 3), single-subject residual dynamic structural equation modelling (RDSEM) [40] will be used in Mplus. We will model the pre- and post-intervention dynamic networks in one SEM model [41]. This allows for statistical testing of the differences between the pre- and post-network estimates.

To explore the biological profile of adolescents and young adults with QFS and compare it with participants with CFS/ME and JIA, as well as healthy controls (objective 4), we will use between-group ANOVAs and/or linear regression analyses.

Exploration of the relationship between individual differences in “fatigue severity” improvement and biological profile changes pre-post interventions (objective 5) will be conducted with growth mixture modelling (GMM) [42] in Mplus.

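### Objective 3 looks for PROfeel's mechanism only in changed network links, so it would miss an effect that runs through a changed level of the targeted factor

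*Protocol article*

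**What the plan says.** Objectives {7} makes objective 3 conditional on PROfeel being effective, and then aims to "investigate through which mechanisms the effects have been reached, by exploring changes in the dynamic ESM networks pre-post intervention".

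Under Intervention description {11a}, the dynamic networks are described as "identifying the contemporaneous and time-lag relations between fluctuations in fatigue and behavior, sleep, social context, cognitions, and feelings". These are links between variables, not average levels.

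Statistical methods {20a} assigns single-subject residual dynamic structural equation modelling (RDSEM) to this objective, for participants who receive PROfeel first. It adds: "We will model the pre- and post-intervention dynamic networks in one SEM model" and "This allows for statistical testing of the differences between the pre- and post-network estimates". The term for what is compared is not defined further, and factor means are not mentioned.

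The advices are illustrated twice. In the section on defining the advice, "an advice could be to reduce rumination time by practicing distracting attention". In {11c}, the illustration of a concrete advice is "cycle to school 3 days a week to increase physical activity".

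The same {20a} section plans the permutation distancing test (PDT) for individual change in fatigue, quality of life and self-efficacy, but not for the factor that an advice targets. Table 1 states that the two ESM phases use the same items.

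**The concern.** The network helps to choose which factor to work on: the section on the feedback report says that figures are selected partly by the weight of the network loadings and their usefulness for an advice. The example advices then try to change how much of that factor occurs. The mechanism analysis asks something else, namely whether the factor has become more or less strongly tied to fatigue.

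These are different quantities. A participant may ruminate less and be less fatigued for that reason, while each unit of rumination still acts on fatigue as before. For that participant the advice has worked as the example intends, and the network comparison has nothing to detect. No other planned test looks at the level of the targeted factor. Because objective 3 is pursued only if PROfeel is effective, this route could go unexamined exactly when it matters, although the data to examine it are in hand.

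**Working it through.** **The plan's own figures.** 4 weeks × 7 days × 5 surveys = 140 surveys per phase. The compliance target is 100 of 140, and 100/140 = 71.4%, which agrees with the stated minimum of 70%.

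**Algebra.** Let R be rumination and F fatigue within one phase, with

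F(t) = a + φ·F(t−1) + b·R(t) + c·R(t−1) + error.

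- Taking means: mean F = [a + (b + c)·mean R] / (1 − φ).
- Subtracting means: f(t) = φ·f(t−1) + b·r(t) + c·r(t−1) + error, where f and r are deviations from the phase mean.

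The second line does not contain mean R. A shift δ in mean R moves mean F by (b + c)·δ/(1 − φ) and leaves φ, b and c as they were. This holds for any values in a linear model.

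**Simulation.** The documents give no network coefficients or VAS variances, so these values are assumptions: contemporaneous link b = 0.4, lagged link c = 0.2, autoregression 0.3 for both variables, innovation SD 12 on a 0–100 scale. There were 140 surveys per phase, 71.4% of records kept, and 600 runs per scenario. The link test is a joint test of phase-by-link interactions in the fatigue equation, using least squares as a stand-in for RDSEM. The level test is a pre-post mean difference with autocorrelation-robust errors.

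Expected fall in fatigue for a 15-point fall in rumination: 0.6 × 15 / 0.7 = 12.9 points. The simulated average was 12.7.

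| Scenario | Link test rejects | Rumination level test rejects | Fatigue level test rejects |
|---|---|---|---|
| No change | 3.8% | 5.7% | 7.2% |
| Level −15, links unchanged | 5.5% | 100% | 99% |
| Same, rumination floored at 0 | 4.5% | 100% | 99.5% |
| Level −40, rumination floored at 0 | 3.8% | 100% | 100% |
| Level unchanged, links halved | 30% | 7.5% | 9.7% |
| Level −15, links halved | 25% | 100% | 72% |

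With 600 runs, the Monte Carlo standard error at 5% is √(0.05 × 0.95/600) = 0.9 percentage points. So 3.8% to 5.5% cannot be told apart from a 5% false-positive rate. The level tests are slightly liberal where the level has not changed, which does not affect the contrast.

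**Sensitivity to the size of the shift.** A second simulation, also with 140 surveys per phase, autoregression 0.3 and a constant link, used response rates of 100% and 71%. The link comparison rejected in 4.4–5.2% of runs (lagged) and 3.9–5.5% (contemporaneous). The level comparison detected a 0.5 SD reduction in 81–89% and a 1 SD reduction in 100%. The power of the level test therefore depends on the assumed shift, but the failure of the link test does not.

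**The case against.** **A reader might infer that the plan would declare that there is no mechanism.** The documents do not support this. The objective is worded as exploration, there is no decision rule, and nothing equates an unchanged network with the absence of a mechanism. What follows is narrower: one route would not be examined.

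**A reader might infer that the advices act only through levels.** That would rest on two illustrations. Advices are individual, may arise from the conversation instead of the figures, and may do more than one thing. The rumination example also tells the participant to "divert attention with an activity on the list" whenever rumination arises outside the scheduled time, which could shorten carry-over or weaken the link to fatigue. In that case the link test has some power, as the last two rows of the table show. This objection stands, and it limits the point to effects through level alone.

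**A level comparison may be intended.** What counts as a network estimate is undefined, the article does not say how the model treats phase means, and the full protocol is not shown. So the comparison is unstated, not excluded. Even so, the article itself fixes the mechanism question as change in the networks and describes those networks as relations between fluctuations. A reader could not infer a test of levels from that.

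**The simulation is circular.** It holds the links fixed and then finds no change in them. This is fair as far as it goes: the algebra carries the argument. The simulation only adds sizes under assumed values.

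**It is tempting to make level change times pre-phase link the main mechanism estimate.** That would treat a within-person observational association as causal and constant, and it would rest on a pre-post contrast with no control. The documents give no basis for ranking it first.

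**Conclusion.** The point holds in limited form. As described, objective 3 compares links only, while the protocol's own examples target levels. An effect that runs purely through the level of the targeted factor would be flagged at about the false-positive rate (3.8–5.5% in the simulations), although a comparison of levels on the same data would usually show it: 81–100% for shifts of 0.5 to 1 SD under the assumed values. When links are halved, the link comparison detects this in about 25–30% of participants, so an unchanged network is weak evidence in that case too.

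That a level shift leaves the links unchanged rests only on linearity. The detection rates rest on assumed coefficients, variances and shift sizes. The objective is exploratory, and neither the primary comparison nor the sample size is affected. The change is worth making because it is cheap and the items are already measured in both phases.

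**What to change.** In {20a}, under objective 3:

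1. For each participant, add to the same pre/post model the change in mean level of the ESM item or items that the advice targets, and of ESM fatigue. Record the targeted items at the feedback meeting.
2. Report these level changes beside the link changes. Do not present a product of level change and link as the main causal estimate.
3. State that unchanged links do not exclude an effect through level.
4. State that the level change is an uncontrolled pre-post contrast, open to time trend and regression to the mean.
5. Report participants whose advice targets no ESM item as not assessable for this route.

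The cost is a few more parameters in a model already planned, one extra entry at the feedback meeting, slightly more output, and a few more exploratory tests per participant. No new visits or measurements are needed.
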